### Intervention and control groups

We will randomly assign participants to EJDeR plus usual care (intervention group) or usual care alone (control group). We chose usual care as the comparator because this reflects current standard care in Sweden where only a minority of parents of persons treated for cancer during childhood receive psychological support after treatment completion; it allows us to assess the feasibility of delivering EJDeR in addition to usual care, and it informs the design of a future superiority RCT comparing EJDeR plus usual care versus usual care alone. Procedures for identifying and responding to participant deterioration or disclosure of risk during the trial are described under Harms.

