##### Telephone guidance

Guidance follows structured LICBT protocols.^60
61^ During the first week of the intervention, the parent guide schedules an initial assessment session (≈45 min) with the parent. The parent guide assesses the participant’s main psychological difficulties and provides the rationale (ie, how the techniques work) for behavioural activation and worry management. Working collaboratively with the participant they agree which LICBT technique to start working with. Participants work through the Introduction and Psychoeducation Module and begin working with the chosen LICBT technique, for example, by reading the workbook, listening to audio recordings of workbook text, and completing exercises. Thereafter, the parent guide provides up to 10 weekly telephone ‘check-in’ sessions (≈15 min) to the participant to review progress, problem-solve any difficulties experienced, and plan next steps. A relapse prevention session (≈30 min) is provided during week 12.

Sessions will be audio recorded (with consent) and we will select a random 15% of recorded sessions to examine parent guide fidelity to the EJDeR guidance protocols. The sampling strategy and fidelity assessment method are described in full in the process evaluation protocol.^53^ Guidance sessions can still take place if the participant does not consent to them being recorded. Parent guides will record data on intervention implementation and self-reported data from participants on intervention engagement in a session log and keep clinical notes to facilitate guidance.

An overview of the EJDeR intervention structure is provided in figure 3. Participants randomly assigned to EJDeR will be able to access usual care.

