### Harms

We define harms as serious adverse events (SAEs), that is, any expected or unexpected adverse event, related, possibly related or unrelated to the EJDeR intervention or the trial, that results in death, a life-threatening adverse event or requires hospitalisation, which includes suicide attempts and self-harm. All SAEs are reported to the principal investigator ([name]).

We will assess SAEs through spontaneous reporting by participants to research team members or parent guides and ongoing monitoring by parent guides during intervention delivery.

A licensed psychologist will train research team members working with recruitment and data collection to identify signs of serious mental illness and/or risk of suicide. In acute situations, for example, where a participant discloses an immediate risk to their safety, research team members will contact emergency services regardless of the participant’s response. In non-acute situations, for example, suicidal ideation without immediate risk, we will inform the participant that we would like a licensed psychologist in our research team to contact them, and, if the parent gives permission, the licensed psychologist will contact them within two working days to conduct a risk assessment. If the participant does not give permission, they are encouraged to contact primary care. If a parent is assessed as needing more support than we can provide within the trial, we will direct them to appropriate mental health services and exclude them from the trial. If a parent guide identifies signs of serious mental illness (including deterioration) and/or risk of suicide, for example, when receiving telephone guidance from the parent guide, the parent guide will conduct the risk assessment immediately and consult with the parent guide supervisor if needed.

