### Outcome data collected for participants who withdraw from trial and/or intervention

All participants will be invited to complete post-treatment (12 weeks) and follow-up (6 months post-treatment) assessments according to the intention-to-treat principle. Participants who withdraw from the intervention but remain in the trial will continue to complete all planned assessments. Participants who withdraw from the trial will not be contacted for further assessments, data collected up to the point of withdrawal will be retained and included in analyses where appropriate.

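### Harms excludes some participants from the trial after randomisation, while the follow-up section promises everyone both later assessments by intention to treat

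*Protocol article*

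**What the plan says.** Under Harms, when a parent is assessed as needing more than the trial can give, "we will direct them to appropriate mental health services and exclude them from the trial". The sentence closes the description of what research staff in recruitment and data collection do, with a psychologist's risk assessment where the parent permits it. The next sentence opens a separate route: "If a parent guide identifies signs of serious mental illness (including deterioration) and/or risk of suicide". That route leads to an immediate risk assessment by the guide and, if needed, consultation with the supervisor. It does not mention exclusion.

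The Intervention and control groups section states: "Procedures for identifying and responding to participant deterioration or disclosure of risk during the trial are described under Harms".

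The section on outcome data for participants who withdraw sets three rules. The general rule is: "All participants will be invited to complete post-treatment (12 weeks) and follow-up (6 months post-treatment) assessments according to the intention-to-treat principle". A second rule keeps in full follow-up anyone who gives up EJDeR alone. The third concerns people who leave altogether by their own choice: "Participants who withdraw from the trial will not be contacted for further assessments".

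The Withdrawal section deals only with the participant's own decision, and separates leaving the intervention from leaving the trial. The Missing data section rules out imputation.

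**The concern.** Removing a randomised person because their mental health has worsened, or their need proves too great, is a removal related to the outcome. It is the kind of loss that intention-to-treat follow-up is meant to prevent. The article promises that follow-up in one section and takes it away in another, so staff facing such a case cannot tell whether the person should still be called at 12 weeks and 6 months.

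Two things are at stake. First, the pilot is meant to supply the variance of the QWB and the between-group difference for a future sample size calculation (Methodological uncertainties). Losing low scorers can move both. Second, ending trial participation ends scheduled assessment of the people whose later course says most about possible harm.

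**Working it through.** **1. Does the rule reach randomised participants?** Yes. The article applies the Harms procedures during the trial. The staff concerned include those collecting data, and data collection runs to 6 months post-treatment. The Eligibility criteria list no such exclusion, so it is not set out as a screening rule.

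**2. Which follow-up rule covers an excluded person?**

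| Status | Later assessments |
|---|---|
| Any participant | Invited to both, by intention to treat |
| Withdraws from the intervention only | Continue |
| Withdraws from the trial | No further contact |
| Excluded by the team | Not covered |

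Under the first row the person is invited; under Harms the person is out of the trial. The two conflict.

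**3. What is lost?** It depends on timing. Exclusion at the inclusion interview or baseline, before allocation, costs nothing in the comparison. Between randomisation and the 12-week call it costs both later QWB scores. At the 12-week call it costs the 6-month score. Nothing is imputed.

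**4. How far could the QWB results move?** The article gives no exclusion rate, so the inputs here are assumptions, apart from n = 30 per arm (Sample size).

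*Mean, fixed gap.* If k of 30 are lost and they average Δ points below the rest of their arm, the observed arm mean rises by kΔ/30. With Δ = 15 and k = 1 to 3 the rise is 15/30 = 0.5 to 45/30 = 1.5 points. With an assumed SD of 12 that is 0.04 to 0.13 SD.

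*Mean and SD, lowest scorers lost.* In 200,000 simulated samples of 30 standard normal scores, with the k lowest removed:

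| k | Rise in arm mean (SD units) | SD of remaining scores (0.99 if none removed) |
|---|---|---|
| 1 | 0.07 | 0.93 |
| 2 | 0.13 | 0.88 |
| 3 | 0.19 | 0.85 |

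*Carry-over to the future trial.* Required n is proportional to the variance. If both arms lost their lowest scorers alike, the shifts in the means would tend to cancel, but the variance would be multiplied by (0.93/0.99)² = 0.88 for k = 1, or (0.85/0.99)² = 0.74 for k = 3. If only one arm did, the equally weighted pooled factor would be (0.93² + 0.99²)/(2 × 0.99²) = 0.94, or (0.85² + 0.99²)/(2 × 0.99²) = 0.87, and the difference would also shift. These are upper-end illustrations, since those excluded need not be the lowest scorers.

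**5. Could the arms differ?** Between randomisation and the 12-week call, an EJDeR participant has one initial session, then "the parent guide provides up to 10 weekly telephone" check-ins, then one relapse prevention session: 1 + 10 + 1 = up to 12 scheduled contacts. A control participant has none. Harms also relies on "ongoing monitoring by parent guides during intervention delivery", which exists in one arm only. Both arms then have the same two assessment calls, and participants in either arm may report spontaneously.

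**6. Could the progression proportions move?** The Sample size section works with 42/60 = 70.0% and 20/30 = 66.7%, that is, everyone randomised. If excluded people were instead dropped from the denominators, the minimum-dose criterion (GO at 65.0% or more) could move either way:
- one exclusion who had not reached the dose: 19/30 = 63.3% becomes 19/29 = 65.5%, from below GO to GO;
- two exclusions who had reached it: 20/30 = 66.7% becomes 18/28 = 64.3%, from GO to below GO.

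**The case against.** A reader might infer that the rule removes deteriorating participants mainly from the EJDeR arm, and so favours EJDeR. The text does not support that as a statement. The exclusion sentence belongs to the research-team route, whose scheduled contacts are the same in both arms, and the guide route does not mention exclusion. The count of 12 contacts against none matters only if cases found by guides also end in exclusion, which is plausible but unstated.

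A reader might also infer that the GO proportions are inflated. The Statistical methods section defines the dose proportion over the intervention group, and the Sample size section uses 30 and 60, so excluded people appear to stay in. In that case an exclusion would, if anything, lower questionnaire completion. Some doubt remains, because the earlier feasibility trial reported completion among those still in the study (42/64 and 40/59, with 75 enrolled) and the 70.0% criterion is taken from that trial.

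Nor is harm simply hidden. Serious adverse events go to the principal investigator, and the steering committee reviews them together with retention. What is lost is scheduled observation after exclusion.

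Finally, this is a descriptive pilot. The QWB difference is not a progression criterion, and progression is a joint judgement. With SD 12 and 30 per arm, the 95% half-width for a between-arm difference is 1.96 × 12 × √(2/30) ≈ 6 points, well above a shift of 0.5 to 1.5. These points limit the consequences. They do not remove the contradiction over who is followed.

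**Conclusion.** The contradiction stands on the text. Harms takes some participants out of the trial, this can happen after randomisation, and the follow-up section promises every participant both assessments with no category for removal by the team. Followed as written, Harms produces an outcome-related loss of QWB data that is not imputed.

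The size cannot be determined, because no exclusion rate is given. With one to three of 30 lost from an arm, the illustrations give a rise in that arm's mean of 0.04 to 0.19 SD and, if the lowest scorers are lost, a fall in its SD from 0.99 to between 0.93 and 0.85. These rest wholly on assumed numbers and an assumed severity of those excluded. Unequal removal between arms is possible but not established, and a shift of the GO proportions in a particular direction is not shown.

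**What to change.** Reconcile the Harms section with the section on outcome data after withdrawal, leaving the clinical referral rule as it is. There are two ways to do so:
- state that exclusion from the trial applies only before randomisation, and list it with the eligibility criteria; or
- separate stopping the intervention from leaving follow-up, so that anyone referred after randomisation stays in the randomised set and all denominators and is still invited to both assessments unless they withdraw.

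In either case, report the number referred or excluded by arm, with the timing relative to randomisation.

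The cost is a rewording of a sentence or two, handled through the amendment route under Protocol changes. The downside is a few more assessment invitations and possibly slightly lower completion figures.

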### Trial timeline

An overview on the trial timeline, that is, the time schedule of pre-enrolment, enrolment and post-randomisation activities is provided in table 3.

**Table 3 T3:** Overview of the trial timeline: pre-enrolment, enrolment and post-randomisation

Timepoint	Pre-enrolment	Enrolment	Post-randomisation		
			Intervention	Post-treatment (12 weeks)	Follow-up (6 months post-treatment)
Identify persons treated for cancer during childhood via the Swedish Childhood Cancer Registry	X				
Identify parents of persons treated for cancer during childhood via the Swedish Tax Agency’s Population Registry	X				
Informed consent	X				
Inclusion interview		X			
Baseline assessment		X			
Randomisation		X			
EJDeR plus usual care			X		
Usual care			X		
**Assessments**					
*Clinical outcomes*					
QWB		X		X	X
PHQ-8		X		X	X
GAD-7		X		X	X
PCL-C		X		X	X
*Health economic outcomes*					
ReQoL-10		X		X	X
RUQ		X		X	X
*Process outcomes*					
TFAQ				X*	
WAI-SR				X*	
Semi-structured interview				X†	

* Intervention group only.

† Semi-structured interviews are described in a separate process evaluation protocol.

GAD-7, Generalised Anxiety Disorder 7-item scale; PCL-C, Post-traumatic Stress Disorder Checklist-Civilian version; PHQ-8, Patient Health Questionnaire 8-item scale; QWB, Questionnaire on Well-Being; ReQoL-10, 10-item Recovering Quality of Life; RUQ, Resource Use Questionnaire ; TFAQ, Theoretical Framework of Acceptability Questionnaire; WAI-SR, Working Alliance Inventory – Short Revised .

### Sample size

We will recruit 60 participants (30 to the intervention group, 30 to the control group), consistent with the median sample size per arm reported for pilot trials.^74^ With 30 participants per group, we can estimate proportions, for example, completion rates, with reasonable precision: 9.0% randomisation rate (approximately 60/667 invited; 95% CI 7.0% to 11.4%), 70.0% completion of all questionnaires at baseline, post-treatment (12 weeks), and follow-up (6 months post-treatment) (42/60; 95% CI 57.4% to 80.2%), and completion of the minimum treatment dose in at least 65% of participants in the intervention group (20/30; 95% CI 46.0% to 83.6%). These estimates will provide adequate information to inform progression decisions.

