### Outcomes

#### Primary feasibility outcomes

Feasibility outcomes relate to procedural, intervention and methodological uncertainties following recommendations for designing and conducting pilot RCTs.^31
51^ We will follow a ‘GO-AMEND-STOP’ progression framework, with STOP indicating ‘do not progress to a future superiority RCT’, AMEND indicating ‘modifications needed to progress to a future superiority RCT’, and GO indicating ‘progress to a future superiority RCT’.^31^
Table 2 summarises feasibility outcomes and progression criteria indicating GO.

**Table 2 T2:** Feasibility outcomes and progression criteria indicating GO

Feasibility outcome	Progression criteria indicating GO	Rationale
Procedural uncertainties		
Proportion invited randomised	≥9.0%	Informed by the enrolment rate (11.0%) found in ENGAGE, with the percentage lowered to account for randomisation potentially leading to lower enrolment rates
Proportion completing all questionnaires at baseline, post-treatment (12 weeks), and follow-up (6 months post-treatment)	≥70.0%	Informed by progression criteria set for ENGAGE
Proportion of responses missing in each questionnaire at baseline, post-treatment (12 weeks), and follow-up (6 months post-treatment)	≤10.0%	Informed by research suggesting missing data ≥10.0% is considered substantial and statistical analysis is likely to be biased^76^
Intervention uncertainties		
Proportion completing the minimum treatment dose	≥65.0%	Informed by research suggesting an average 64.0% of participants adhere to guided web-based mental health interventions^77^

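### The 95% CI printed for minimum treatment dose completion (20/30; 46.0% to 83.6%) does not follow from 20/30; the method that reproduces the other two planning intervals gives 48.7% to 80.9%

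*Protocol article*

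**What the plan says.** The Sample size section sets the target: "We will recruit 60 participants (30 to the intervention group, 30 to the control group"). It justifies this first by the median arm size of pilot trials and then by the precision with which three feasibility proportions could be estimated:

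- randomisation: "9.0% randomisation rate (approximately 60/667 invited; 95% CI 7.0% to 11.4" (percent);
- completion of all questionnaires: "42/60; 95% CI 57.4% to 80.2" (percent);
- minimum treatment dose: "completion of the minimum treatment dose in at least 65% of participants in the intervention group (20/30; 95% CI 46.0% to 83.6" (percent).

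No interval method is named for any of them. The paragraph ends: "These estimates will provide adequate information to inform progression decisions". In Table 2 (Primary feasibility outcomes) the matching GO criterion reads "Proportion completing the minimum treatment dose ≥65.0" percent.

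**The concern.** Three intervals in one sentence, at one confidence level and for the same kind of quantity, should come from one calculation. The third does not fit with the other two, and its limits do not look like any usual 95% interval for 20 out of 30.

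What is at stake is limited but real. These intervals are the quantitative part of the sample size justification. The affected figure belongs to the only intervention criterion in Table 2. Minimum dose completion is also one of the two matters that fell short of GO in the ENGAGE feasibility trial and led to this pilot. A reader who recomputes the figure will find that it fails, and cannot tell from the text whether the count, the denominator, the method or the confidence level was meant to be different.

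**Working it through.** **Inputs** (all from the Sample size section): 60/667, 42/60 and 20/30, with their printed limits. Confidence is 95%, taken as two-sided because both limits are given, so z = 1.96 and z² = 3.8415.

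**Step 1. Identify the method from the two companion intervals.** Agresti-Coull uses ñ = n + z², p̃ = (x + z²/2)/ñ, and limits p̃ ± z√[p̃(1 − p̃)/ñ].

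- 60/667: ñ = 670.84; p̃ = 61.92/670.84 = 0.0923; half-width 0.0219. Result 7.04% to 11.42%; printed 7.0% to 11.4%. Match.
- 42/60: ñ = 63.84; p̃ = 43.92/63.84 = 0.6880; half-width 0.1136. Result 57.43% to 80.16%; printed 57.4% to 80.2%. Match.

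The 42/60 interval separates the methods: Wilson gives 57.49% to 80.10%, Wald 58.4% to 81.6%, exact 56.8% to 81.2% and Jeffreys 57.7% to 80.5%. None of these rounds to the printed pair.

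**Step 2. Apply the same method to 20/30.** ñ = 33.84; p̃ = 21.92/33.84 = 0.6478; half-width 1.96 × √(0.6478 × 0.3522/33.84) = 0.1609. Result 48.7% to 80.9%. Printed: 46.0% to 83.6%. No match; each limit is off by 2.7 points.

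**Step 3. Try other methods, and exactly 65% of 30 (19.5/30).**

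| Method | 20/30 (%) | 65% of 30 (%) |
|---|---|---|
| Wald | 49.8–83.5 | 47.9–82.1 |
| Wald, continuity-corrected | 48.1–85.2 | 46.3–83.7 |
| Wilson | 48.8–80.8 | 47.1–79.5 |
| Wilson, continuity-corrected | 47.1–82.1 | 45.5–80.8 |
| Agresti-Coull | 48.7–80.9 | 47.1–79.5 |
| Exact (Clopper-Pearson) | 47.2–82.7 | 45.5–81.4 |
| Jeffreys | 48.9–81.4 | 47.2–80.1 |
| **Printed** | **46.0–83.6** | |

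For 20/30, mid-P, logit, arcsine, t-quantile Wald and inversion of the exact binomial test also fail. No lower limit for 20/30 falls below 47.1%, while the printed one is 46.0%. The next lower count, 19/30, does not help either (Wald 46.1% to 80.6%, exact 43.9% to 80.1%).

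The closest candidate overall is continuity-corrected Wald at a nominal 65%: 0.65 ± [1.96 × √(0.65 × 0.35/30) + 1/60] = 0.65 ± 0.1873, that is 46.3% to 83.7%. It misses the lower limit by 0.3 and the upper by 0.1, and it is not an interval for 20/30.

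**Step 4. Size of the discrepancy.** Printed width 83.6 − 46.0 = 37.6 points. Agresti-Coull 80.9 − 48.7 = 32.2; excess 5.4. Exact 82.7 − 47.2 = 35.5; excess 2.1.

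**Step 5. Direction.** The printed interval is wider than the recomputed one at both ends, so it understates the precision that 30 participants provide.

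**The case against.** The best defence is that this is an illustrative planning figure in a condensed article and that it errs on the cautious side. Replacing it changes no sample size, threshold, analysis or progression rule. All of that stands, and it limits the weight of the point. It does not make the figure right.

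A reader might infer more from the error than the documents support.

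- *That the adequacy statement fails.* The correction narrows the interval, so it cannot count against that statement. Adequacy is asserted rather than shown, but it is not refuted: with 30 participants the chance of seeing at least 20 completers is 4.9% at a true rate of 50% and 97.4% at 80%. Statistical methods already commits to reporting this proportion with a 95% CI. The section on deciding about progression weighs the criteria together with other feasibility outcomes, the process evaluation and the trial steering committee. Further operating characteristics could sit in the analysis plan, which is not shown.
- *That the sample size rests on these intervals alone.* It does not; the median arm size of pilot trials is cited first.
- *That the GO rule misclassifies average performance.* Table 2 explains the threshold as "Informed by research suggesting an average 64.0% of participants adhere to guided web-based mental health interventions". A true rate of 64% lies below 65.0%, so failing to reach GO is what the rule asks for. A roughly even chance at the cut-off itself (50.8% at a true 65%) is a property of any threshold, and setting the target one point above an average is a design choice.
- *That 20/30 contradicts 65%.* 65% of 30 is 19.5, so 20 is the smallest count that meets a minimum of 65%. The text is consistent here.

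**Conclusion.** The point holds as an arithmetic error confined to one interval. The limits 46.0% to 83.6% do not follow from 20/30, or from 65% of 30, by any method tried. By the method that reproduces both companion intervals, the figure should be 48.7% to 80.9%, and the printed interval is about 5 points too wide. By the exact method it should be 47.2% to 82.7%, and the excess is about 2 points.

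This rests on two assumptions: that the intervals are two-sided 95% intervals for a single proportion, and that one method was meant for all three. The second is an inference from the match in the companion figures, since the article names no method. The finding that the printed limits are wrong does not depend on it; only the choice of replacement does. How the printed limits arose cannot be established from the document.

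The error is conservative, and the criticism stops at the figure itself and the unnamed method. It is a correction to make, not a reason to doubt the design.

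**What to change.** In the Sample size section, restate the third interval as 20/30 = 66.7%, 95% CI 48.7% to 80.9%, and name the interval method once for all three figures (Agresti-Coull, if that is what was used). If the sponsor prefers another method, recompute all three with it. Use the same named method when the proportions are reported at the end of the trial.

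Keep the GO criterion as a percentage (≥65.0%). Rewriting it as a fixed 20 of 30 would fail whenever the arm is not exactly 30. The Recruitment timeline section itself anticipates about 54 to 63 randomised in total, and in ENGAGE the dose denominator was 71 although 72 gained access to the intervention.

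The cost is a change of wording: no further participants, and no change to thresholds, analyses or progression rules.
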